## Methods and analysis

### Study design

The PROMISS trial is a multicentre RCT designed to examine the effectiveness of personalised dietary advice aiming at increasing protein intake and advice on optimising the timing of protein intake in close proximity of usual physical activity on change in physical functioning after 6 months. Participants will be randomised into three groups: one control group (no intervention); intervention group 1 receiving personalised dietary advice aiming at increasing protein intake to at least 1.2 g/kg aBW/day; and intervention group 2 receiving personalised dietary advice aiming at increasing protein intake to at least 1.2 g/kg aBW/day, including personalised advice to optimise the timing of protein intake in close proximity of usual physical activity.

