### Randomisation, allocation and masking

Randomisation by means of a stratified block randomisation procedure will be performed by an independent statistician. Participants will be allocated in a 1:1:1 ratio to the three groups. The size of the randomisation blocks is three. Participants will be stratified according to their baseline habitual protein intake (<0.9 or 0.9–1.0 g/kg aBW/day) and sex to ensure homogeneous distribution of baseline habitual protein intake and sex in the three groups across the two recruitment sites, because there may be a different intervention effect by baseline habitual protein or sex. In case couples are eligible, we will allocate them to the same intervention group to limit interference between intervention groups. We will randomly select on which partner the randomisation for the intervention group is based. Any resulting unbalance in the number of subjects per treatment arm will be corrected in the randomisation of the next block. Due to the nature of the study, researchers, nutritionists and participants are not blinded to the study group.

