Participants in intervention group 2 will receive the same dietary advice as intervention group 1, and the personalised advice to consume at least 7.5–10 g protein through protein-(en)rich(ed) food products within half an hour after performing usual physical activity as this may enhance resistance exercise-induced MPS.^27^ One RCT among older adults has shown that protein supplementation in combination with resistance exercise had beneficial effects on, for example, muscle mass and function, but no differences in effect were found between protein consumption pre-resistance versus post-resistance exercise.^43^ We therefore recommend protein intake after physical activity as this is a uniform and more feasible advice compared with ‘in close proximity of’, and might also result in less stomach discomfort as compared with protein consumption prior to physical activity. Usual physical activity is defined as either physical exercise (eg, biking, swimming, tennis) or the most intensive activities of daily living when the participant does not engage in physical exercise (eg, gardening, housekeeping, doing groceries) for a minimum of 30 min. The advice is linked to most extensive or longest physical activity. Participants are instructed not to become more or less physically active but merely to shift their physical activity or protein intake moment.

During the intervention period, nutritionists will plan follow-up phone calls in consultation with the participants during week 2, week 4, week 8, week 16 and week 20 to ask if they have understood the advice and are able to adhere to the advice. In addition, any issues related to the use of protein-enriched food product can be discussed (intervention groups only). If necessary, changes in the dietary advice will be made, for example when weight change >2 kg has occurred (based on self-assessment). Participants allocated to the control group do not receive any intervention, but are contacted on similar time points as the intervention groups to ask how they are doing.

All participants are invited to a minimum of one organised lecture on non-health-related themes and other social events during the trial in order to stimulate their commitment to the trial. Separate lectures/events (with the same topic) are organised for the intervention groups and the control group to prevent interference between intervention arms. Participants can freely attend those lectures and all travel costs will be reimbursed.

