#### Statistical analyses plan

Statistical reporting will be according to the Consolidated Standards of Reporting Trials standards.^70^ The collected data at the two study sites will be pooled together at the Amsterdam site, with a variable indicating study site. All statistical analyses on primary and secondary outcome measures will be performed by an independent statistician blinded for group allocation. Baseline characteristics will be described (percentages, means±SDs) by study group.

The primary analyses will be based on the intention-to-treat principle, that is, data from participants allocated to the intervention groups will be analysed as part of those groups, irrespectively of their level of adherence to the advice. Multiple imputation using Multivariate Imputation by Chained Equations will be used to impute missing cost and effect data. The continuous primary outcome (change in 400 m walk time) will be analysed using mixed model regression analyses with study site as random variable. We will adjust for baseline 400 m walk time as well as baseline protein intake (g/kg aBW/day) and sex (the stratification factors for randomisation). We will compare intervention effects of the respective intervention groups versus the control group. Effects will also be expressed in Cohen’s d and the corresponding 95% CIs will be calculated, which allows comparison between intervention effect estimates between different outcome measures. The secondary outcomes and other measures will be analysed using mixed model regression analogously to the primary outcome. For binary secondary outcomes, generalised estimating equation models will be used. With regard to time-to-event analyses (incident sarcopenia risk and mobility limitations) Cox proportional hazard models will be used. Time-to-event is defined as the time of the start of the study period to the date of the first occurrence of the event (3-month follow-up visit or 6-month follow-up visit). Participants who do not meet these criteria will be censored at the latest time we had information available. We will perform subgroup analyses stratified by baseline protein intake (<0.9 or 0.9–1.0 g/kg aBW/day), sex and baseline 400 m time (based on median) for the primary and secondary outcomes.

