Per-protocol analyses will also be conducted as a sensitivity analysis. Effect estimates for change in primary and secondary outcome measures will be calculated for participants from the intervention groups who reached the protein target of at least 1.2 g/kg aBW/day after both 3 and after 6 months (mean protein intake based on the three 24-hour dietary recalls) versus participants from the control group. Data will be analysed using SPSS (IBM SPSS Statistics, Version 26). A two-sided p value of 0.05 is considered statistically significant.

The cost-effectiveness analysis will be performed from a healthcare perspective. Total mean costs during the study will be related to physical functioning (the 400 m walk test) and change in quality-adjusted life-years based on the EuroQol 5D Questionnaire. Mixed model regression analyses will be used to estimate differences in the primary outcome of the respective intervention groups versus the control group. Linear regression analyses will be used to estimate differences in QoL (expressed as quality-adjusted life-years) and healthcare costs. Incremental cost-effectiveness ratios will be calculated by dividing the difference in costs by the difference in effects. Statistical uncertainty will be estimated using bias-corrected accelerated bootstrapping (5000 replications) and will be presented using cost-effectiveness planes and cost-effectiveness acceptability curves.

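### The cost-effectiveness analysis names only control as comparator, so the group 2 ratio does not show what the timing advice adds to the advice it shares with group 1

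*Protocol article*

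**What the plan says.** The Study design section sets out three arms, and the randomisation section adds: "Participants will be allocated in a 1:1:1 ratio to the three groups". The arms are nested. The Intervention section says: "Participants in intervention group 2 will receive the same dietary advice as intervention group 1", to which the timing advice is then added.

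In the Statistical analyses plan section, the clinical analysis names one comparator: "We will compare intervention effects of the respective intervention groups versus the control group". The cost-effectiveness paragraph repeats it for walk time: "Mixed model regression analyses will be used to estimate differences in the primary outcome of the respective intervention groups versus the control group". The following sentence says that linear regression will estimate differences in QALYs and healthcare costs, and names no comparator. The ratio is then defined: "Incremental cost-effectiveness ratios will be calculated by dividing the difference in costs by the difference in effects". Uncertainty is to come from 5000 bias-corrected accelerated bootstrap replications, shown on cost-effectiveness planes and acceptability curves.

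The article gives no comparison of group 2 with group 1 on costs, effects or their ratio. It does say, in its list of strengths and limitations and again in the Discussion, that the trial addresses what timing adds to physical functioning.

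**The concern.** A decision-maker can adopt only one of the three options. With more than two exclusive options, an option's incremental ratio is normally taken against the next less costly option that is not dominated. Here that step would show what the timing add-on costs per unit gained beyond the advice alone.

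Against control, group 2 carries the whole benefit of the advice that group 1 also delivers. Its ratio is an average over the shared advice and the add-on, and hardly moves with the value of the add-on. If the acceptability curves are also drawn arm by arm against control, each gives the probability that one arm beats control. Neither gives the probability that each option is the best of the three.

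**Working it through.** **The plan's own figures.** The document gives no number for the economic analysis. The sample size does reproduce: 2 × (1.960 + 0.842)² × 61² / 28² = 74.5, so 75 per group. The total of 225 / 0.85 is 265 against the stated 264, a rounding difference. No stated number is wrong. The 75 per group is used below.

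**Inputs.** The nested arms and the control comparator come from the document. All costs, QALY gains, standard deviations and the threshold of 50,000 per QALY are assumed, because the document gives none.

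**Check 1: does the ratio against control respond to the add-on?** Ratio = difference in cost / difference in effect. Assume group 1 against control is +200 and +0.020 QALY, a ratio of 10,000. Vary group 2:

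| Group 2 against control | Ratio against control | Group 2 against group 1 |
|---|---|---|
| +300, +0.030 | 300/0.030 = 10,000 | 100/0.010 = 10,000 |
| +220, +0.0205 | 220/0.0205 = 10,732 | 20/0.0005 = 40,000 |
| +300, +0.021 | 300/0.021 = 14,286 | 100/0.001 = 100,000 |
| +300, +0.019 | 300/0.019 = 15,789 | dearer and less effective: dominated |

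The middle column stays within 10,000 to 15,789. The right-hand column runs from equal value to dominated.

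**Check 2: are the arms mis-ranked?** Assume group 1 at +200 and +0.010 QALY, and group 2 at +400 and +0.012 QALY. The ratios against control are 200/0.010 = 20,000 and 400/0.012 = 33,333, both under 50,000. Group 2 against group 1 is 200/0.002 = 100,000, above it. Net benefit against control at 50,000 is 500 − 200 = 300 for group 1 and 600 − 400 = 200 for group 2. The control-based figures therefore already place group 1 first.

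**Check 3: pairwise and joint probabilities.** Assume gains of 0.010 QALY in both arms, costs of 200 and 250, a per-person net-benefit SD of √(4000² + 2000²) = 4,472, and 75 per arm. Mean net benefit against control is 300 and 250. The standard error of a difference is 4,472 × √(2/75) = 730. Pairwise probabilities of beating control are Φ(300/730) = 66% and Φ(250/730) = 63%. By simulation of the three arm means, the probabilities of being the best option are 20% (control), 42% (group 1) and 38% (group 2). Both pairwise figures exceed one half, yet no option has an even chance of being best. The order of the two intervention arms is the same on both scales.

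**Check 4: precision of group 2 against group 1.** Taking the plan's SD of 61 s and 75 per arm for walk time, the standard error is 61 × √(2/75) = 9.96 s and the 95% CI half-width is 1.96 × 9.96 = 19.5 s. Power for an assumed difference of 14 s or 7 s is about 29% or 10%. Adjustment for baseline walk time may narrow this.

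**The case against.** Control is named expressly only for walk time. The sentences on QALYs and costs, on the ratio, and on planes and curves name no comparator. This stands: for QALYs and costs, control is a reading from context, though it is the only comparator in the paragraph. A reader might also infer that the plan specifies two separate curves against control. It does not say so, and the point about curves is conditional on that construction.

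A journal article may leave ordering and dominance rules to a fuller plan. That is fair for those details taken alone. But the article does name the comparator, and the one it names does not fit three nested options.

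A reader might infer that the plan will recommend the wrong arm. Checks 2 and 3 do not support this: group 1 stays ahead of group 2 on control-based figures. The group 2 versus group 1 point estimate also follows by subtracting the two control contrasts, and the document states no threshold or adoption rule. What cannot be recovered from the two contrasts is the joint uncertainty, because they share a control group.

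The cost gap may be small. The timing advice is given at the same consultation meeting (Study timeline) with the same follow-up calls (Intervention), and the cost list under Secondary outcomes names only care use. This stands as a limit on size.

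Finally, the secondary objectives that include healthcare costs are worded for the protein advice alone, and the statements about what timing adds concern physical functioning. That lowers the priority. It does not make a control-based ratio for group 2 informative about the add-on.

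**Conclusion.** The point holds in a limited form. As written, the economic analysis names only control as comparator, and a group 2 ratio on that basis does not show what the timing advice buys beyond group 1. If the curves follow the same basis, they will not show how likely each of the three options is to be best. Under assumed inputs the ratio against control can sit near 10,000 to 16,000 while the add-on ranges from equally good value to dominated. The actual distortion cannot be computed from the document and may be slight. The conclusion rests on reading control as the comparator for QALYs and costs as well as walk time. No wrong recommendation has been demonstrated, and the primary analysis is untouched. This is an inexpensive improvement to a secondary analysis.

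**What to change.** In the cost-effectiveness paragraph, specify a fully incremental analysis for both walk time and QALYs. Order the three arms by mean cost, remove dominated and extendedly dominated arms, and report each ratio against the next less costly remaining arm. Where both intervention arms remain, this includes group 2 against group 1. From the same 5000 bootstrap replications, with all three arms resampled together, show one acceptability curve giving each arm's probability of the highest net benefit. Name the comparator for QALYs and costs explicitly, and keep the ratios against control as supplementary. A group 2 versus group 1 contrast on walk time in the clinical analysis would not by itself achieve this, since the cost difference, the ratio and the curves would be unchanged.

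The cost is a few sentences and a few lines of code on replicates already planned, with no new data. The downside is that the group 2 versus group 1 result will be imprecise. It should be reported as an estimate with its uncertainty, not as a test.

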### Participants’ safety

In case any (medical) questions arise during the screening or intervention period, participants can consult an independent medical doctor. All adverse events and serious adverse advents will be tracked by the nutritionists during the follow-up phone calls, 3-month follow-up visit and 6-month follow-up visit to assess their potential relationship to the intervention at both sites and will be documented in the final report. Adverse events will be reported within 7 days (death or life-threatening situations) or within 15 days (in case of other adverse events) of first knowledge to The Medical Ethical Committee of the Amsterdam UMC, location VUmc (required for the Dutch site only).

### Data quality assurance and data management

Research data will be collected at each site and each visit (baseline, 3-month follow-up visit and 6-month follow-up visit) using a standardised protocol with the same order of assessments, and entered two times in separate electronic datasets. When discrepancies between the datasets are found, the original questionnaire will be consulted. Questionnaire items and measurements will include the corresponding variable names to minimise errors in data entering. Finally, the two final electronic datasets (one from each site) containing all data will be pooled. A data catalogue and codebook will be developed.

Original questionnaires will be stored in a secure manner at each site in an area with limited access. All records that contain names (ie, informed consent forms) will be stored separately from study records identified by code number. All databases will be secured with password-protected access systems.

### Patient and public involvement

The PROMISS RCT is designed by the Faculty of Science (VU Amsterdam, the Netherlands) and the Department of General Practice and Primary Health Care (University of Helsinki, Finland) (please see online supplemental appendix 1 for the PROMISS trial group), a collaboration of the EU Horizon 2020 PROMISS Project. Two medical and one ethical advisor are involved in the study. As part of the PROMISS project, we previously performed three pilot studies as a preparation of the long-term PROMISS randomised trial, of which one is published.^71^ We included the feedback of the participants in designing the long-term PROMISS randomised trial; participants enjoyed participating in the pilot studies and they liked the frequent contact with the nutritionist. We also tested which protein-enriched food products they preferred and included those products in the long-term PROMISS randomised trial which they liked the most. Older adults are not involved in recruitment of participants or conduct of the study. Results of this study will be disseminated to participants through sending them a lay abstract with the results and conclusions of the study. At the end of the study, each participant will receive a fact-sheet with personal results of dietary intake data, hand grip strength, body composition measures and BW. Participant burden of the pilot intervention was assessed using informal feedback from older adults participating in one of three pilot studies.

10.1136/bmjopen-2020-040637.supp1Supplementary data

### Ancillary studies

Within the PROMISS trial, three ancillary studies will be conducted: (1) persuasive technology study, (2) microbiota study and (3) functional MRI (fMRI) study.

#### Persuasive technology study

The primary aim of this study is to examine the effect of persuasive technology on adherence to the personalised dietary advice aiming at increasing protein intake to at least 1.2 g/kg aBW/day in a subsample of Dutch participants from intervention group 1 (n=24) and intervention group 2 (n=24), that is, the first 24 participants of intervention group 1 and the first 24 participants of intervention group 2 that consent to it (written informed consent will be signed).

Participants will be provided with a food storage box that registers which provided protein-enriched food products are taken out. The food box is used to store the protein-enriched food products provided by the research team. Participants will also receive a tablet that allows participants to register any consumed protein-enriched food products and supports them in finding alternative food products that contain a comparable amount of protein. For this, the system uses the personalised dietary advice as provided by the nutritionist and data from the storage box. The tablet application aims to stimulate adherence to the dietary advice by providing tailored and personalised messages. In addition, personality characteristics and communication style preferences that are determined via a questionnaire completed at baseline are used to tailor the style and tone of these messages.^72^

In addition to the personalised messages, half of the participants from intervention groups 1 and 2 who participate in the persuasive technology substudy will also receive a gamified version of the tablet application (n=12+n=12). In this version, participants can earn game points by registering their consumed protein-(en)rich(ed) food products and by playing mini-games about the protein content of foods (ie, guess the protein content, more-or-less protein). The distribution of receiving the gamified version versus standard version is quasi-randomised, where we will balance the group size.

At the consultation meeting, participants receive their food storage box and tablet. Both are fully configured, that is, they are loaded with their personal dietary advice. After the 6-month follow-up visit, participants will be asked to return the equipment and fill out questions on the feasibility and user experience of the provided persuasive technology.

The secondary objectives are (1) to investigate to what extent participants perceive messages of which the style and tone are adapted to their personal characteristics as personalised and adequate, and (2) to determine the effect of gamification on the effectiveness and feasibility of the persuasive technology.

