**Methods and analysis:**

The PRevention Of Malnutrition In Senior Subjects in the EU (PROMISS) trial examines the effect of personalised dietary advice aiming at increasing protein intake with or without advice regarding timing of protein intake to close proximity of usual physical activity, on change in physical functioning after 6 months among community-dwelling older adults (≥65 years) with a habitual protein intake of <1.0 g/kg adjusted (a)BW/day. Participants (n=264) will be recruited in Finland and the Netherlands, and will be randomised into three groups; two intervention groups and one control group. Intervention group 1 (n=88) receives personalised dietary advice and protein-enriched food products in order to increase their protein intake to at least 1.2 g/kg aBW/day. Intervention group 2 (n=88) receives the same advice as described for intervention group 1, and in addition advice to consume 7.5–10 g protein through protein-(en)rich(ed) foods within half an hour after performing usual physical activity. The control group (n=88) receives no intervention. All participants will be invited to attend lectures not related to health. The primary outcome is a 6-month change in physical functioning measured by change in walk time using a 400 m walk test. Secondary outcomes are: 6-month change in the Short Physical Performance Battery score, muscle strength, body composition, self-reported mobility limitations, quality of life, incidence of frailty, incidence of sarcopenia risk and incidence of malnutrition. We also investigate cost-effectiveness by change in healthcare costs.

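### The persuasive-technology study states a causal primary aim but gives the device to the first consenters with no stated comparator, so any estimate of its effect on adherence is confounded

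*Protocol article*

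**What the plan says.** The Protocol article, under Persuasive technology study, opens with a causal aim: "The primary aim of this study is to examine the effect of persuasive technology on adherence to the personalised dietary advice". The device is a food storage box that registers what is taken out, plus a tablet. Its purpose is explicit: "The tablet application aims to stimulate adherence to the dietary advice by providing tailored and personalised messages". The users are Dutch participants only, chosen by order of consent: "the first 24 participants of intervention group 1 and the first 24 participants of intervention group 2 that consent to it". No comparison group is named for this aim.

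Half of the users in each intervention group (12 + 12) also get a gamified version. On how that half is chosen, the section says: "The distribution of receiving the gamified version versus standard version is quasi-randomised, where we will balance the group size". This split serves a secondary objective, "to determine the effect of gamification on the effectiveness and feasibility of the persuasive technology".

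Three other sections matter. Sample size gives 44 participants per study group per site. Study timeline and Compliance have dietary intake measured by three 24-hour recalls before the 3- and 6-month visits in the trial as a whole, so adherence is also known for intervention participants without a device. Statistical analyses plan fits a mixed model with study site as random variable, adjusted for baseline walk time, baseline protein intake and sex.

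**The concern.** An effect of the technology on adherence needs people with and without it who are otherwise alike. The selection rule prevents that, and it is fixed in this document. A later analysis plan can name a comparator but cannot make it a randomised one.

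Each available comparator has its own problem:

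- **Dutch intervention participants without a device.** If exactly 24 of 44 in a group consent, the non-users are all refusers. If everyone consents, they are all later enrolees. In between, they are a mixture. Willingness to accept an adherence aid is plausibly related to adherence itself. Calendar time may matter too, since Recruitment and screening lets the protein-screener threshold vary between >15% and >30% with the response to recruitment.
- **Finnish intervention participants.** Site and device are completely tied together, because no Finnish participant receives one.

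The gamified comparison could have been clean, since both versions go to people who have already consented. Quasi-randomisation with balancing of group size leaves room for the assignment to be predicted, in a study where staff are unblinded.

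At stake is a substudy conclusion that the technology raises or does not raise adherence. For the main trial, the matter is what the intervention effect is said to consist of.

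**Working it through.** **Inputs.** From Persuasive technology study: 24 device users in each intervention group, Dutch site only; 12 + 12 of them gamified. From the abstract and Sample size: 88 per group, 44 per group per site; target difference 28 s, SD 61 s, two-sided α = 0.05, power 0.80, drop-out 15%. The article gives no sample-size basis for this substudy.

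**The plan's own figure.** n per group = 2 × (1.960 + 0.842)² × (61/28)² = 74.5, so 75, as stated. Then 225/0.85 = 264.7, against the stated 264. The main-trial numbers reproduce to within rounding.

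**Share of participants with a device.**
- All intervention participants: 48/176 = 27.3% (24/88 in each group).
- Dutch intervention participants: 48/88 = 54.5% (24/44 in each group).
- Finnish participants and controls: 0%.
- Dutch intervention participants without a device: 44 − 24 = 20 per group, 40 in total.

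**Detectable standardised difference at 80% power**, before drop-out: d = (1.960 + 0.842) × √(1/n₁ + 1/n₂).

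| Comparison | n₁ vs n₂ | d |
|---|---|---|
| Device vs Dutch non-users, as planned | 48 vs 40 | 0.60 |
| The same within one intervention group | 24 vs 20 | 0.85 |
| Gamified vs standard | 24 vs 24 | 0.81 |
| Randomised 1:1, all 88 consent | 44 vs 44 | 0.60 |
| Randomised 1:1, 60 consent (assumed) | 30 vs 30 | 0.72 |
| 48 devices among 60 consenters (assumed) | 48 vs 12 | 0.90 |

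The planned 48 vs 40 split and a randomised 44 vs 44 split have the same nominal sensitivity. The defect is how the users are selected, not how many there are. The last two rows show why a fixed 48 devices is a poor basis for randomising: the article gives no consent rate, and if few more than 48 consent, hardly any consenters are left as controls. With exactly 48 there are none.

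**Possible influence on the main trial.** If the device changed walk time among its users by an assumed 5, 10 or 20 s, an intervention-group mean would move by 48/176 of that: 1.4, 2.7 or 5.5 s, against the 28 s target. The documents give no estimate of such an effect.

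**The case against.** The case on the other side is substantial, and much of it stands.

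- **The device is planned.** It is listed as an ancillary objective in the Introduction, appears in Table 1, and is described with numbers, content, timing and consent. A reader might call it an unplanned co-intervention; the document does not support that.
- **The aim is not wholly out of reach.** Recalls in all participants allow a comparison with about 40 Dutch non-users, which removes site as a confounder. A reader might infer that the aim cannot be addressed at all. In fact an observational estimate is available; what is not available is an unconfounded one.
- **The main comparison is not broken.** The device is handed out at the consultation meeting, after randomisation, with the same planned number in both intervention groups. Intention-to-treat against control remains a randomised comparison. A reader might also infer that site differences in effect become uninterpretable, but no site-by-treatment analysis is planned; such a difference would be confounded with device exposure, no more.
- **An article may leave detail out.** A device term or sensitivity analysis in the main model may sit in a fuller document, so its absence is not counted here. The selection rule and the quasi-randomised split are stated outright, and they are what the point rests on.
- **The gamified split is small and secondary, and openly called quasi-randomised.** That is so, but it does not make the allocation sound, and the trial already has an independent statistician for its main randomisation.

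**Conclusion.** The point holds for the ancillary study. Its primary aim is worded as an effect, its users are the earliest consenters in each Dutch intervention group, and no comparator is stated. Any contrast with non-users mixes the device with consent and calendar time, or with site. The direction and size of that bias cannot be computed from the document. The gamified comparison of 24 versus 24, sensitive only to differences of about 0.81 SD, carries an avoidable allocation weakness as well.

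For the main trial the consequence is one of description. The intention-to-treat effect is valid, but it is the effect of advice plus an adherence device in 27% of intervention participants, all Dutch. It is not the effect of advice alone. On the assumed device effects above, the shift in a group mean is small beside 28 s.

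The percentages assume that recruitment meets 44 per group per site and that all 48 device places are filled. The detectable differences use a normal approximation and ignore drop-out.

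**What to change.** 1. **Gamified versus standard:** allocate from a concealed random list stratified by intervention group. This needs a list and a sentence in the protocol.
2. **Primary aim, one of two routes:**
   - Randomise consenting Dutch intervention participants to device or no device within intervention group, for example 1:1, with the number of devices set by the number of consenters and at most 48. Compare protein intake at 3 and 6 months between the randomised consenters. The cost is a short amendment, some consenters without a device, and precision that depends on consent (about 0.60 SD only if all 88 consent, 0.72 with 60).
   - Or restate the aim as feasibility, or as an exploratory association with no causal claim. This costs only wording, and is the only route left if the devices have already been handed out.
3. **Main trial:** describe the intervention effect as advice plus a device in about a quarter of recipients.
4. **If the device's influence on the primary outcome is examined:** estimate the intervention effect within each site against that site's own randomised controls, labelled exploratory. Precision is limited: 44 versus 44 detects 2.802 × 61 × √(2/44) = 36.4 s before drop-out, and a difference between sites would still mix device with site. Do not drop device users from the intervention groups alone. With no matching exclusion from control, that would bring selection into the randomised comparison, and would cut each intervention group from 88 to 64 (about 54 after 15% drop-out; power about 0.73 for 28 s against 75 controls).
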